### Recruitment of participants

Potential participants will be recruited by several means. An advertisement (hard copy and electronic form) will be posted around the University of Otago Wellington (UOW), Massey University, Victoria University of Wellington, Wellington Hospital, and the wider District Health Board. In addition, the New Zealand College of Clinical Psychologists and the New Zealand Psychological Society will be approached to attract the interest of clinical psychologists, either in-training or in-post.

The participant information sheet and consent form will be sent to those responding to the advertisement for further consideration. Prior to admission to the research studies, potential participants will also be screened to ensure they meet the inclusion/exclusion criteria.

Screening will be undertaken online (on the survey platform *Qualtrics*) using a brief bespoke questionnaire collecting information on all but two of the inclusion/exclusion criteria (see below) and using the following tools for the remaining criteria:
*The Somatosensory Amplification Scale* (SSAS) (a brief, 10-item questionnaire: approximately 2 min to complete [36]);*The Edinburgh Handedness Questionnaire* [37] (a brief version of this self-report tool will be used: approximately 1 min to complete [38]).

Recruitment of potential participants began in November 2018 and will continue until April/May 2019. Random group allocation will not begin until the middle of May 2019.

### Eligibility criteria

#### Inclusion criteria

Participants must satisfy the following conditions:
Currently enrolled on a full time medical, nursing or allied healthcare degree/diploma OR already qualified and working as a doctor/nurse/allied healthcare professional;Aged 18–35 years. This range is based on indications of declining interoception after approximately 40 years of age [39], and initial declines in RTs have been identified as early as 24 years of age [40]; hence, age is capped at 35 to limit such heterogeneity within the sample;BMI must be equal to or lower than 30 (i.e. non-obese) or 32 for Maori/Pacific Islanders. Increased body fat percentage tends to make interoception more difficult [41];Regular levels of physical activity: at least 150 min of moderate-intensity aerobic physical activity throughout the week or least 75 min of vigorous-intensity aerobic physical activity or an equivalent combination of moderate- and vigorous-intensity activity (based on the *World Health Organization* guidelines). Regular exercise influences autonomic tone [42, 43], which is able to improve interoceptive accuracy as assessed by heartbeat perception [44–46];Normal or corrected vision;Normal or corrected hearing;Right-handed (left vs. right-handed people respond differently on RT tasks; see for example [47]; plus, this criterion removes the need for bilateral counterbalancing);Availability for the entire study period, including attendance at two laboratory sessions (one in May/June 2019, one in July/August 2019, with an 8-week interval between sessions).

#### Exclusion criteria

Poor physical health (including gastrointestinal disorders, heart disease, kidney disease, respiratory disease);Poor psychological, psychiatric, or neurological health (e.g. alexithymia, schizophrenia, depression, anxiety, brain injury);Somatosensory amplification (score on the SSAS > 35);In pregnancy;Formal dance or drama training (see [48]);Formal musical training (see [49]);Formal meditation or mindfulness training (> 4 weeks consecutively over the past year) (see [7]).

Besides the case of pregnancy, which will likely affect physiological measurement, gender will not be part of the screening, despite men tending to outperform women in interoceptive sensitivity tasks (e.g. cardiac activity detection), due to the likely explanation for this difference being varying BMI across the sexes (see [50]).

### Randomisation

Each participant will be assigned a number ID in order of recruitment into the study. Once the required sample size has been reached and scheduling completed for laboratory attendance, these numbers will be entered into an online random number generator (http://www.randomization.com/) to allocate these numbers into one of the three blocks (cardioception group; gastroception group; control group). The allocation ratio for the groups will be 1:1:1.

Other randomisation pertains to counterbalancing over trials and blocks of trials. This will be undertaken to control for ordering effects and will be achieved using the standard functions of the stimulus presentation software programme *SuperLab (Version 6, Cedrus)*.

Participants will be told of their allocation immediately after the completion of baseline data collection. Concealment will be ensured using sealed notes provided during this first laboratory visit, within the process described below (see the “Confidentiality and single blinding” section).

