### Spatial cueing task

One of the interoception groups will show significantly faster reaction times (RTs) and greater response frequency to emotional stimuli regardless of cue type compared with each of the other groups after baseline; plus, there will be a greater change between baseline and follow-up. Each of the interoception groups separately and combined will show significant differences from the control group.One set of cues for the same group (i.e. the interoception group in (1)) will facilitate significantly faster RTs and greater response frequency. This set will match the target area of the body for that group (i.e. a chest cue for the cardioception group; a lower abdomen cue for the gastroception group). The “matching” cue for the other interoception group will not facilitate faster RTs or greater response frequency. If any cue facilitates faster RTs or greater response frequency for the other groups, it will be the same cue that facilitates for the interoception group in (1).This same group will display greater within-group coherence in the location of the body indicated to be active during trials compared with the other groups after baseline. It will also show the greatest change between baseline and follow-up compared with the other groups.This same group will report greater intensity compared with the other groups after baseline. It will also show the greatest change between baseline and follow-up compared with the other groups. The interoception groups combined will report greater intensity than the control group.This same group will show greater heart rate deceleration after baseline following the presentation of emotional stimuli compared with the other groups; both interoceptive groups will show greater heart rate deceleration than the control group.

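### Batch allocation after full recruitment does not balance age, which the protocol ties to reaction time, and the listed predictors omit it: a small, avoidable loss of precision in the after-baseline RT contrasts

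*Protocol article*

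**What the plan says.** Under Randomisation, numbers are assigned in order of recruitment and allocation waits for the full sample: "Once the required sample size has been reached and scheduling completed for laboratory attendance, these numbers will be entered into an online random number generator". Recruitment of participants confirms the timing: "Random group allocation will not begin until the middle of May 2019". The only constraint given is the ratio: "The allocation ratio for the groups will be 1:1:1". No stratification or minimisation is described.

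Screening precedes allocation and is done online, "using a brief bespoke questionnaire collecting information on all but two of the inclusion/exclusion criteria". The two exceptions are somatosensory amplification and handedness, which have their own tools. Age and BMI therefore fall under the questionnaire.

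The Inclusion criteria explain the age limits partly by RT: "initial declines in RTs have been identified as early as 24 years of age". Of BMI they say: "Increased body fat percentage tends to make interoception more difficult". RT is the primary outcome (Dependent variables, both tasks). The predictor lists for both tasks and for the spatial cueing task include group, time, the interoception measures, heart phase, valence and cue factors, but neither age nor BMI.

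Hypothesis 1 compares RTs "compared with each of the other groups after baseline" and adds a comparison of change. Hypothesis 6 does the same for the stop/signal task.

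**The concern.** In most trials participants arrive one at a time and balance on a covariate has to be built in as they come. Here everyone is known before the list is drawn, so balance on a known factor costs almost nothing. The protocol itself names age as related to the primary outcome within the eligible range. Of the 18 eligible years of age, 11 (25 to 35) lie beyond 24, so the cap narrows the spread without removing it.

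At stake is precision, and how convincing the after-baseline RT comparisons will be in a small three-arm trial. A visible age gap between arms would invite doubt about which arm is really faster, and Hypotheses 2 to 6 and 8 follow the arm that leads in Hypothesis 1.

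**Working it through.** **Inputs from the protocol.** Target 70 in total, so 23/23/24; planned minimum 54, so 18 per arm; partial eta-squared 0.15, alpha 0.05, power 80%; control RT SD 780.6 ms after treatment (all from Sample size). The protocol gives no age-RT correlation. Below, age is assumed to explain 5% or 10% of RT variance, that is r = √0.05 = 0.224 or √0.10 = 0.316.

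**1. The plan's own figure.** f² = 0.15/0.85 = 0.1765. For a group-by-time test with 2 numerator degrees of freedom, the large-sample noncentrality for 80% power is 9.635, so N = 9.635/0.1765 = 54.6. This rounds up to 55, close to the stated 54. A noncentral F calculation gives 58, which 70 less 5 to 10 drop-outs (60 to 65) still covers. The contrast that sizes the trial is thus group by time.

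**2. Chance of an age imbalance.** The difference between two arm means of a standardised covariate has SD √(2/n).

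| Per arm | SD of a pairwise difference | P(some pair of the three arms differs by at least 0.5 SD) |
|---|---|---|
| 18 | √(2/18) = 0.33 | 29% |
| 23 | √(2/23) = 0.295 | about 21% |
| 23/23/24 | – | 20% |

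The last column is by simulation with a normal covariate; the 23/23/24 row used 40,000 random splits.

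**3. What such a gap does to an after-baseline RT contrast.** A gap of 0.5 SD in age shifts the RT difference by 0.5 × r:
- 5% explained: 0.5 × 0.224 = 0.11 SD, or 0.112 × 780.6 = 87 ms.
- 10% explained: 0.5 × 0.316 = 0.16 SD, or 0.158 × 780.6 = 123 ms.

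With one RT summary per participant, the standard error of the unadjusted contrast at 23 per arm is 0.295 SD. The shifts are therefore 0.112/0.295 = 0.38 and 0.158/0.295 = 0.54 standard errors. The millisecond values borrow the SD of the cited meditation study and only indicate scale.

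**4. What it does to the change contrast.** If age adds the same amount b × age to a participant's RT at baseline and follow-up, the change is (RT₂ + b × age) − (RT₁ + b × age) = RT₂ − RT₁. A stable additive age effect drops out of the group-by-time term.

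**5. Validity.** With covariates explaining 20% of variance, simulated type I error without adjustment was 5.0% (18 per arm) and 4.7% (23 per arm), against 5.1% and 4.9% with adjustment. The test keeps its size.

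**6. Value of adjusting.** Expressed as participants: 70 × (1/(1 − R²) − 1).
- R² = 0.05: 70 × (1/0.95 − 1) = 3.7, about 4.
- R² = 0.10: 70 × (1/0.90 − 1) = 7.8, about 8.

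These apply to an after-baseline contrast not adjusted for baseline RT. Baseline RT already carries much of any stable age effect, so the gain is smaller once it is in the model.

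**The case against.** The strongest reply is that nothing here is wrong. Simple randomisation is valid, chance imbalance is already in the standard error, and stratification is optional. The age cap was set to limit this heterogeneity. Hypotheses 1 and 6 pair each after-baseline contrast with a change contrast, the trial is sized on treatment by time, and the GEE covers both time points with interactions. All of this stands, and it is why the point is minor.

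The article is also condensed, and an analysis plan that is not shown could add covariates. That weakens the remark on the predictor list. It does not touch the allocation method, which the protocol fixes.

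A reader might go further and infer that age, BMI, activity and sex all drive RT, and so quote a 49% or 59% chance of imbalance on at least one of three or four factors. The protocol does not support this. It ties only age to RT. BMI and physical activity are tied to interoception, as is sex, whose effect the Exclusion criteria attribute to BMI, so it is not an independent fourth factor. The same section says gender is not part of screening. Nor are Hypotheses 3 to 5 RT outcomes: they concern location, intensity and heart rate deceleration.

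**Conclusion.** The point holds as a modest, near-free improvement. The whole sample and its screening data are in hand before a single allocation on bare ID numbers. The protocol says RT performance changes with age inside the eligible range, yet age is neither balanced nor listed as a predictor.

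A reader might take this for bias in deciding which arm looks best. It is not: type I error stays near 5%. The loss is in the precision of the after-baseline RT contrasts in Hypotheses 1 and 6, with about a 20% chance of an age gap of at least 0.5 SD between some pair of arms. It largely cancels from the group-by-time contrast.

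The gain of about 4 or 8 of 70 participants rests on the assumed 5% or 10% of RT variance and shrinks with baseline adjustment. The true gain cannot be derived from the document. The point also assumes that screening records age and BMI as values and not only as meeting the limits.

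**What to change.** Split the screened list by age (for example up to 24 and 25 to 35) and run the random allocation within each part, keeping 1:1:1. Include age as a fixed covariate in the RT models, preferably as a continuous variable, since two strata leave some imbalance within them. For the interoception outcomes of Hypothesis 7, also include screening BMI.

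If the list has already been drawn, only the covariate part remains, and it should be fixed before results by group are seen.

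The cost is about an hour of statistical work, one or two degrees of freedom, a slightly more complex allocation list, and arm sizes that may differ slightly where a stratum does not divide by three. No participant's schedule changes.

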### Participant retention

The likelihood of drop-out from the project will be reduced by offering compensation (supermarket vouchers) for the time commitment to the project, in addition to the attraction of meditation training, maintaining regular contact either by face-to-face (laboratory visits) or online monitoring (on *Qualtric*s), offering flexibility to participants on laboratory scheduling, and limiting the sample to those who are likely to be already on-site (either the University campus or Hospital, which are interconnected buildings).

### Study setting/location

Given the need to undertake laboratory tasks and the use of physiological measures, coupled with the local sampling possibility, all in-person data collection will take place in the Centre for Translational Physiology, University of Otago Wellington (UOW).

### The intervention

For those allocated to the experimental groups, an intervention involving one of two interoceptive practices will begin immediately after completing baseline measurements in the laboratory. Data will be collected at baseline and again 8 weeks later (a time scale based on a previous study of body awareness and interoceptive accuracy [7]).

Over the 8-week period, participants from each of the experimental groups will be instructed to log on to *Qualtrics* 6 days per week to record their responses to several qualitative questions on their everyday emotional experiences, and then to attend to their assigned body area for 20 min (2 × 10 min) after responding to these same questions (see Additional file 1 for the wording presented to the three groups). The 20-min period will be timed automatically with full task instructions provided. Participants will be requested to do this task at a set time each evening. All log-ins and time spent on the site will also be recorded and time stamped automatically, which will help with adherence, create a sense of connection for participants throughout the study period (in the absence of a bespoke class or programme to attend in person, participants will at least know their online attendance is monitored), and ensure that the task proceeds similarly for all participants. Adherence will also be encouraged by contacting all participants at the mid-point (i.e. 4 weeks after baseline) to check for problems or difficulties in adhering to the intervention instructions.

The instructions for cardioception will be to focus on the inside of one’s chest area without using non-interoceptive cues, throughout the daily 20-min period. These participants will be provided with an image of a human body with a highlighted chest area, which displays the target area for interoceptive focus i.e. (a limited area around the heart's location). The instructions for gastroception will be to focus on sensations in the lower abdomen (i.e. the dominant locus of gastrointestinal structures and activity). These participants will again be provided with an image of a human body, but with a highlighted lower abdominal area, displaying the target area for interoceptive focus. Importantly, this does not, then, incorporate the mouth and—in particular—the oesophagus, which overlaps with the location of the heart and would, therefore, be confounding as a focal point. Given the dominance of the lower abdomen for gut volume/activity, there is arguably relatively little *detectable* activity throughout much of the mouth/oesophagus unless a participant is experiencing gastric reflux, vomiting, or other pain, or is eating/has just eaten, which the sample screening aims to preclude in any case.

All participants from the experimental groups will be required to not undertake any additional meditation outside of the intervention, during the 8 weeks.

### Rationale for the control group

The control group participants will differ from the experimental groups only by their not undertaking meditation/interoception training during the 8 weeks. They will otherwise be “active”, i.e. they will be asked to log on to *Qualtrics* 6 days per week for 8 weeks to complete the self-reflection questionnaire. This will control for any effect of self-reflection or regular engagement in a task; it will measure any effect of interoceptive training in general, as well as any effect of each specific form of interoceptive training. The interoceptive groups together will also act as their own control for a merely general effect of interoception. If they choose to receive them, controls will be provided with the online meditation instructions and task once their participation is complete.

### Data collection procedures

#### Pre-laboratory

Prior to lab attendance at baseline and follow-up, participants will provide online (via *Qualtrics*) self-report measures on emotion regulation and health. The self-report tools to be used are the *Difficulties in Emotion Regulation Scale*, the *Emotion Reactivity Scale*, and *SF-36* sub-scales (outlined below in the “Descriptions of self-report tools for outcome measures (emotion regulation and interoceptive sensibility)” section). On an on-screen image of a human body, participants will also click to indicate the location(s) where they most tend to detect emotional feeling. If they do not detect emotional feeling in any part of the body, then no response is required. This is intended to identify the dominant areas of the body prior to entry into the study.

Other pre-task procedures will include providing instructions to participants stating that during the 4 h prior to their arrival they should not consume a heavy meal (but are adequately sated by the time of arrival in order to avoid distracting or facilitating hunger pains) or items containing caffeine or nicotine, or a large quantity of water (i.e. just maintain usual drinking amounts to prevent differences between participants in body awareness during the laboratory visit, such as awareness of the stomach or bladder), nor should they have consumed alcohol in the previous 24 h. In advance of attending, each participant will be asked (using the *SF-36*) if they have been experiencing any pain over the previous 4 weeks (which may interfere with their performance or that may prove distracting).

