### Sample size

A power analysis calculation was based on reaction time (RT) measures in Silverstein et al. [34], who reported a mean RT of 2134.1 ms (SD = 856.6 ms) pre-treatment and 1403.6 ms (SD = 462.3 ms) post-treatment for meditators, and 1865.1 ms (SD = 800.4 ms) pre-treatment and 1893 ms (SD = 780.6 ms) post-treatment for controls. This gave a treatment-by-time partial eta-squared of 0.15, with a *p* value of 0.03. Using the same partial eta-squared for the three group, two time point studies, with alpha = 0.05 and 80% power, a minimum of 54 participants would be required in total (across all group conditions). This equates to a minimum of 18 participants per group to detect the main effect in the spatial cueing task. (regarding the stop/signal task, Verbruggen and De Houwer [35] detected effects in a single group with a sample size of 23 participants.) We will aim for 70 participants in total, assuming a drop-out buffer of approximately 5–10 participants. This will allow 20+ participants in each group.

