## Data analysis

Generalised Estimating Equations (GEE) will be used to analyse the two data points, including variable interactions. GEE can account for repeated measures as well as the potential problem that the primary outcome variable (RT) may not be normally distributed (although it will be continuous). Using GEE, the effects of the predictors on RT can be modelled under different circumstances, and the interrelationships between predictors can also be investigated. Significance testing will be undertaken at the *p* < 0.05 level.

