## Limitations

There are several limitations of the current design.

For the spatial cueing task, attempts have been made to make all trials comparable in terms of timings, regardless of response. However, on trials where no emotion is detected, there will be a maximum of 6 s to respond before the next trial; but on trials where there is a response, the timing may be longer if a participant takes time to consider their response, or shorter if a participant becomes fatigued and aims to rush through the trials by clicking in response to all stimuli. In order to prevent the former problem, participants will be instructed to respond as quickly as possible (to reduce the effect of cognitive appraisal). In relation to the latter problem, the use of catch trials and emotionally neutral trials will indicate this trend in a participant’s data (which can then be excluded from analysis).

Secondly, the effect of a negative stimulus in the spatial cueing task may take time to dissipate (i.e. the refractory period). Hence, there may be carry-over from one trial to the next. This limitation is addressed to a degree by having a mixture of negative and neutral stimuli, plus varied levels of standard arousal (i.e. based on previous studies of rated responses to images on the IAPS and NAPS). Plus, the time to respond in full to each stimulus before experiencing the next stimulus may approach the end of a refractory period in any case, and between blocks, there will be self-directed rest periods.

Thirdly, there is a possibility that presenting the same set of emotional stimuli over the two data points—in both main tasks—will result in habituation across the two presentations. There is, however, a low probability of this given the brief presentation of each stimulus, plus an 8-week gap between data points, and the use of the IAPS, which has been shown to resist habituation.

There is likely to be some degree of self-selection bias in the sample, given the wholly voluntary nature of the recruitment, both in terms of consenting to participate and trial completion.

Finally, as a preliminary trial, there will only be recruitment of a non-suicidal sample. This will not itself allow findings on emotion regulation to be directly related to suicidality.

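### The week-8 emotion-regulation scales are online but scheduled only as a step before the laboratory visit, so people who do not return would be lost from Hypothesis 8 unnecessarily

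*Protocol article*

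**What the plan says.** All statements are in the protocol article.

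- **Timing of the scales.** Pre-laboratory, on the DERS, ERS and SF-36 sub-scales: "Prior to lab attendance at baseline and follow-up, participants will provide online" (via Qualtrics). The MAIA is completed within the laboratory session, after the water load test.
- **Follow-up.** There is one post-baseline time point: "Data will be collected at baseline and again 8 weeks later" (The intervention). The text before the self-report tool descriptions treats follow-up as returning to the laboratory and going through everything again.
- **Expected loss.** The target is 70 participants, "assuming a drop-out buffer of approximately 5–10 participants" (Sample size).
- **Selective completion.** Limitations says some self-selection is likely, "both in terms of consenting to participate and trial completion". No arm or direction is given.
- **Adherence data.** "All log-ins and time spent on the site will also be recorded and time stamped automatically" (The intervention).
- **Analysis.** "Generalised Estimating Equations (GEE) will be used to analyse the two data points, including variable interactions" (Data analysis). No working correlation, weighting or analysis set is named.
- **Use of the scales.** Hypothesis 8 compares each trained group with control on the DERS, the ERS and SF-36 emotional well-being.

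**The concern.** Hypothesis 8 carries the trial's link from interoceptive training to emotion regulation, and so to RQ4 on suicide prevention. Its outcomes are the easiest in the trial to collect, because a participant can complete them anywhere. Tying them to attendance means that someone who will not come back is likely to supply no week-8 score, although only the laboratory measures require presence.

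The loss may not be neutral. The trained groups carry a practice burden that controls do not: 20 min × 6 days × 8 weeks = 960 min, or 16 h. If people leave because the practice did nothing for them, the trained completers are a favourable subset. If people leave for other reasons, the distortion may vanish or run the other way. Scores that were never requested cannot be recovered by any later analysis.

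**Working it through.** **1. The plan's own figures.** Inputs from Sample size: partial eta-squared 0.15, alpha 0.05, power 80%, three groups, stated minimum 54.

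- f² = 0.15/0.85 = 0.1765, with a 2-df group-by-time test and noncentrality f² × N.
- The large-sample chi-square version gives N = 55 (power 79.5% at 54), so 54 is reproduced closely. The noncentral F version gives N = 58 (77.0% at 54).
- Planned loss is 5/70 = 7.1% to 10/70 = 14.3%.
- Inflating 54: 54/(1 − 0.0714) = 58.2, so 59; 54/(1 − 0.1429) = 63.
- A target of 70 covers this. With 65 or 60 completers, power is 85% or 82% by noncentral F.

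The buffer is therefore adequate for power on the reaction-time effect it was sized for. It does not address who leaves.

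**2. What needs a visit and what does not.**

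| Outcome | Visit needed? | Scheduled |
|---|---|---|
| DERS, ERS, SF-36 | No, online | Before the laboratory visit |
| MAIA | No, it is a questionnaire | Inside the visit |
| Reaction times, ECG, heartbeat and water load tests | Yes | Inside the visit |

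**3. Size if leavers are non-practisers with no benefit.** Let d be the fraction lost from the trained arms, with controls lost at random. Then the effect in all randomised = (1 − d) × completer effect + d × 0, so the completer effect is the all-randomised effect × 1/(1 − d).

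- Loss equal by arm: 1/(1 − 5/70) = 70/65 = 1.08; 1/(1 − 10/70) = 70/60 = 1.17.
- All loss in the two trained arms taken together, 70 × 2/3 = 46.7 people: d = 5/46.7 = 0.107 gives 1.12; d = 10/46.7 = 0.214 gives 1.27.

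**4. Other mechanisms.** The protocol gives no effect size, correlation or adherence rate for these scales. The following are assumptions: true effect 0.50 SD (scored so that higher is better), baseline/follow-up correlation 0.6, 80% practisers, no benefit in the rest. The estimates are simulated group-by-time contrasts with 2,000,000 per arm. The percentages are the loss in each arm that loses people.

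| Who leaves | 7.1% loss | 14.3% loss |
|---|---|---|
| Random, both arms | 0.50 | 0.50 |
| Non-practisers from the trained arm, controls at random | 0.54 | 0.58 |
| Low baseline from the trained arm, controls at random; independence working correlation | 0.59 | 0.66 |
| The same, exchangeable working correlation | 0.50 | 0.50 |
| Low outcome, both arms equally | 0.50–0.51 | 0.51 |
| Low outcome, control arm only | 0.35–0.41 | 0.24–0.33 |

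The second row is the same under either working correlation and agrees with step 3 (0.50 × 1.08 = 0.54; 0.50 × 1.17 = 0.58). The last row is an understatement. Both the size and the sign depend on facts that the protocol does not supply.

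**The case against.** The strongest reply is that this reads too much into a condensed article. The scales are online and come before the visit, so missing the visit need not lose them. Nothing says that stopping the practice ends follow-up or that the week-8 link is withheld. All participants are contacted at four weeks about adherence problems, and Participant retention lists vouchers, regular contact and flexible scheduling. Missing-data handling may sit in an analysis plan that is not shown.

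Much of this stands, and it rules out three stronger readings that a reader might infer.

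- *That the training effect is overstated.* The documents give no loss by arm or by reason. Controls also have a log-in task 6 days a week for 8 weeks. Participant retention counts the appeal of meditation training as a reason to stay, which could hold the trained arms better, although controls are offered it afterwards.
- *That the analysis is an ordinary, unweighted GEE, valid only if loss is completely at random.* Data analysis names GEE and nothing more. Silence on weighting or working correlation is not a choice of the weakest option. Loss that depends on baseline did no harm in the exchangeable case above.
- *That stopping practice means withdrawal.* No section says so.

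What the reply does not meet is the collection schedule. Whom to ask for an outcome, and when, is fixed in the article itself. It attaches forms that need no visit to a visit that some participants are expected to miss.

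**Conclusion.** The point holds as a weakness in the stated collection procedure, not as a demonstrated bias. With 5–10 of 70 expected to leave and completion conceded to be partly self-selected, the schedule as written risks losing week-8 emotion-regulation scores that could be had without a visit.

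Under the single assumption that all leavers are non-practisers with no benefit, the inflation is 8–17% with equal loss by arm. It reaches at most 27% if all 10 losses fall in the trained arms taken together, and that figure stacks worst-case assumptions. Under other plausible patterns the bias is nil or reversed. The case for acting rests on the low cost of the remedy and on its working in either direction, not on a predicted sign. The conclusion covers Hypothesis 8 and, through the MAIA, the sensibility part of Hypothesis 7. It does not extend to laboratory reaction times.

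**What to change.** State in the data-collection section that:

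1. the week-8 DERS, ERS and SF-36 link goes to every randomised participant on a date fixed from their baseline visit, whether or not they still practise or will attend the laboratory;
2. the MAIA is offered online to those who do not attend, with place of completion recorded;
3. all randomised participants are analysed in the group to which they were allocated.

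Keep GEE. A simple sensitivity analysis for informative loss, using the time-stamped log-ins, is optional. Replacing the main method is not warranted. Weights estimated from 5–10 losses would be fragile, and a mixed model that includes baseline would not cure the loss of people who did not benefit.

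The cost is one automated Qualtrics message and a few sentences of text, with no extra visit or staff. The drawback is that a few MAIA forms will be completed away from the laboratory. The gain is limited to those who reply, and the laboratory outcomes remain exposed to the same loss.
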